#### Adverse events

Patients will be informed that Adverse Events, Serious Adverse Events and Suspected Unexpected Serious Adverse Reactions must be reported as soon as possible to their ENT-surgeon or research nurse. Additional queries are made at 3, 6, 9 and 12 months to ensure that they did not fail to report occurrences. These events will be registered throughout the trial in Castor EDC. Each serious adverse event must be reported to the sponsor within 24 hours after the physicians’ knowledge. In the event that patient safety is compromised, patients can be unblinded.

#### Cost-effectiveness

Cost-effectiveness will be assessed from both a healthcare and societal cost-utility perspective, where cost per avoided vertigo attack and cost per Quality Adjusted Life Year (QALY), respectively, will be used as the metrics. MD-related medical expenses, other healthcare expenses and the cost of lost productivity will all be included in the estimated societal cost, which will be calculated using the iMTA Medical Consumption Questionnaire (iMCQ) and IMTA Productivity Cost Questionnaire (IPCQ).

### Statistical analysis

Ordinal regression using mixed model analysis will be used to analyse the primary outcome (ie, class of vertigo). In addition, generalised estimating equation analysis of the actual vertigo attacks recorded using the DizzyQuest app will be used to estimate the incidence rate ratio for comparison between the methylprednisolone and placebo groups. A decrease of 100% is considered total control of vertigo episodes, while a reduction of >40% is considered a substantial and thus clinically relevant reduction.^17^

Mixed model analysis will be used to analyse differences in the questionnaire scores (DHI, TFI, FLS, eQ-5D/VAS, iMCQ, iPCQ) between the two groups. Logistic regression analysis will be used to analyse the remaining secondary outcomes (incidence of escape interventions, hearing loss and adverse events). A reduction in hearing of 10 decibels or a 15% change in word recognition will be regarded as a clinically significant difference.^17^

Subgroup analyses will be performed with regard to sex, duration of the disease and the type of MD (delayed MD, familial MD and autoimmune MD). These subgroups will be defined as described in Frejo *et al*.^25^ Two sensitivity analyses will be carried out in addition to the intention to treat analysis: a per protocol analysis in which patients who received additional co-interventions to achieve vertigo control are excluded; and an as-treated analysis in which participants who received additional co-interventions are analysed.

In order to evaluate the average costs and outcomes between the methylprednisolone and placebo groups for the cost-effectiveness analysis, intention-to-treat and net-benefit analysis will be used. For all statistical analysis, multiple imputation to adjust for missing data will all be used.^26^ QALYs will be calculated using the Dutch tariff for the EuroQoL EQ-5D-5L^23^ and as sensitivity analysis, the visual analogue scale valuing health, with power-transformation.^27^ All outcomes with corresponding statistical analysis methods are summarised in table 2. A p value <0.05 will be considered as statistically significant for all analyses and will be performed using SPSS V.25 or higher (SPSS Chicago Illinois, USA).

**Table 2 T2:** Outcomes with corresponding statistical analysis method

	Outcome	Type of data	Analysis
Primary outcome	Number of spontaneous vertigo attacks, lasting more than 20 min	Count	Generalised estimating equation
	AAO HNS (1995) class of vertigo		Mixed model analysis
Secondary outcomes	Hearing (PTA; 0.5, 1, 2, 3 kHz and SDS)	Continuous	Logistic regression analysis
	Tinnitus (TFI)	Categorical	Mixed model analysis
	Quality of life (DHI, TFI, FLS, eQ-5D/VAS)	Categorical	Mixed model analysis
	Use of escape medication and co-interventions	Count	Logistic regression analysis
	(S)AE	Binary	Logistic regression analysis
	Cost effectiveness (iMCQ, iPCQ)	Categorical	Mixed model analysis

DHI, Dizziness Handicap Index; EQ 5DEuroQol 5DFLS, Functional Level Scale; iMCQ, iMTA Medical Consumption Questionnaire; iPCQ, iMTA Productivity Cost; PTA, pure tone average; (S)AE, (Serious) Adverse EventSDS, Speech Discrimination ScoreTFITinnitus Functional Index

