**Methods and analysis:**

We aim to recruit 148 patients with unilateral MD from six hospitals in the Netherlands. Patients will be randomly assigned to either the methylprednisolone or the placebo group. Two injections will be given, one at baseline and one after 2 weeks. Follow-up assessments will be done at 3, 6, 9 and 12 months. The primary outcome will be the frequency of vertigo attacks. Attacks will be evaluated daily with the DizzyQuest app. Secondary outcomes include hearing loss, tinnitus, health-related quality of life, use of co-interventions and escape medication, (serious) adverse events and cost-effectiveness. These will be evaluated with audiometry and multiple commonly used, validated questionnaires. For the primary and secondary outcomes mixed model analysis, generalised estimating equation analysis and logistic regression analysis will be used.

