### Sample size

A sample size calculation was performed based on recommendations as summarised in the Clinical Practice Guideline for Menière’s disease.^1^ An expected proportion of subjects achieving vertigo control of 87.5% was assumed for methylprednisolone treatment compared with an assumed 67.5% for placebo, that is, a difference in treatment effect of 20%. With a statistical power (1-β) of 80% and a type 1 error (α) of 5%, 67 patients per group are required. With an estimated 10% loss-to-follow-up, 74 patients will be included in each arm, giving a total sample size of 148. In total, over the six participating centres, 340 MD patients yearly visit the Otolaryngology department and will be screened for the trial. It is expected that 15% will meet the inclusion criteria and will be willing to participate. This will result in approximately 50 eligible patients for inclusion per year.

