### Outcome measures

#### Vertigo

The primary outcome measure will be defined by the class of vertigo as defined by the AAO HNS 1995 guideline. The class of vertigo is defined by the average number of attacks per month during 6 and 12 months after treatment divided by the number of attacks 6 months before treatment times 100. As a result, the following class of vertigo is defined:

A: Complete control of vertigo=0.B: Substantial control of vertigo=1–40.C: Limited control of vertigo=41–80.D: Insignificant control of vertigo=81–120’.E: Worse control of vertigo >120.

Moreover, the daily attack vertigo frequency will be monitored with the aid of the DizzyQuest app (Psymate 2).^18 19^ The DizzyQuest app will be used to track the primary outcome measure, the frequency of dizziness attacks. Patients will answer daily questionnaires about their health and well-being and patients can report vertigo attacks at any time using the DizzyQuest app. Additionally, the Dizziness Handicap Inventory (DHI) questionnaire will be administered at baseline, after 6 months and after a year to assess how dizziness affects daily life.^20^ The effect of the injections in the DHI will be reported as raw data, as well as change in handicap category (mild handicap, moderate handicap or severe handicap) related to improvement, unchanged or worsened.

The following secondary outcomes will be measured.

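### Two different outcomes are labelled primary with no rule for deciding between them, and the 80% power belongs to a third, binary outcome that has no listed analysis

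*Protocol article*

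**What the plan says.** The protocol article describes the primary outcome in several places, and they do not agree.

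- **Abstract, Methods and analysis:** "The primary outcome will be the frequency of vertigo attacks".
- **Outcome measures, Vertigo, opening sentence:** "The primary outcome measure will be defined by the class of vertigo as defined by the AAO HNS 1995 guideline".
- **Same section, further down:** "The DizzyQuest app will be used to track the primary outcome measure, the frequency of dizziness attacks".
- **Statistical analysis:** "Ordinal regression using mixed model analysis will be used to analyse the primary outcome (ie, class of vertigo"). The next sentence adds the count: "In addition, generalised estimating equation analysis of the actual vertigo attacks recorded using the DizzyQuest app will be used to estimate the incidence rate ratio".
- **Table 2:** the first primary row is "Number of spontaneous vertigo attacks, lasting more than 20 min", analysed by generalised estimating equations (GEE). The AAO-HNS class, analysed by a mixed model, follows it, still ahead of the secondary outcomes.

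The significance rule is common to everything: "A p value <0.05 will be considered as statistically significant for all analyses".

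The Sample size section uses a different, binary quantity: "An expected proportion of subjects achieving vertigo control of 87.5% was assumed for methylprednisolone treatment compared with an assumed 67.5% for placebo". The Patient safety section says the interim analysis is on the primary endpoint, and then states its limits as differences in vertigo control. Neither the Statistical analysis text nor Table 2 lists an analysis of that proportion.

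**The concern.** The count and the class are not two names for one thing. The class is a five-level banding of each patient's attack rate after treatment relative to that patient's own rate before it. The GEE compares recorded attack counts between arms as a rate ratio. They can point different ways: a few patients with very many attacks can dominate a rate ratio while barely moving a class distribution.

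With two primary outcomes the plan has to say what counts as a positive trial: either one, both, or one decisive and the other supportive. It does not say. A reader of the results could not tell whether a significant finding on one outcome alone meets the stated objective, and the choice could look driven by the data. The stated power also describes a comparison that neither primary analysis makes.

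**Working it through.** **1. The plan's own sample size.** Inputs from the Sample size section: p1 = 0.875, p2 = 0.675, difference 0.20, power 80%, α = 5% (taken as two-sided). The mean proportion is 0.775.

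n per arm = [1.96·√(2·0.775·0.225) + 0.842·√(0.875·0.125 + 0.675·0.325)]² / 0.20²
= (1.1575 + 0.4826)² / 0.04 = 67.2.

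Power at 67 per arm is 79.9%. With 10% loss, 67/0.9 = 74.4, against 74 stated. The figure reproduces as a comparison of two proportions.

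**2. Error rate if success on either primary outcome counts.** Two two-sided tests at 0.05, with test statistics bivariate normal with correlation ρ under the null. Familywise error = 1 − P(|Z1| < 1.96 and |Z2| < 1.96). The document gives no ρ, so a range is shown.

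| Assumed ρ | Familywise error |
|---|---|
| 0 | 9.75% |
| 0.5 | 9.1% |
| 0.8 | 7.8% |
| 0.9 | 7.0% |

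**3. Power if both must succeed.** The error rate stays within 5%. If each test has 80% power, joint power = P(Z1 < 0.842 and Z2 < 0.842).

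| Assumed ρ | Joint power |
|---|---|
| 0 | 64% |
| 0.5 | 69% |
| 0.8 | 73% |
| 0.9 | 75% |

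**4. Power of the ordinal analysis at 67 per arm.** The document gives no class distribution. For illustration only, classes A and B together are set to 67.5% on placebo and 87.5% on methylprednisolone, and one ordinal comparison stands in for the mixed model.

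- *Proportional odds.* OR = (0.875/0.125)/(0.675/0.325) = 3.37. Whitehead's formula: power = Φ(ln OR·√V − 1.96), with V = (134/12)(1 − Σp̄³), where p̄ is the mean class proportion over the two arms. For placebo classes A to E of 30, 37.5, 15, 10 and 7.5%, V = 9.76 and power = Φ(1.215·3.124 − 1.96) = 97%. Two other assumed placebo distributions give 94% and 97%.
- *The same 20-point gain placed differently.* Placebo as above; active-arm classes C to E at 6, 4 and 2.5%. Simulated Wilcoxon tests (4,000 runs each) give 34% with A/B at 30/57.5%, 62% at 40/47.5%, and 92% at 55/32.5%.

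**5. Power of the count analysis at 67 per arm.** A negative-binomial approximation with assumed mean μ, dispersion k and rate ratio RR: variance of ln RR = [(1/μ + k) + (1/(μ·RR) + k)]/67; power = Φ(|ln RR|/√variance − 1.96).

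- μ = 8, k = 1, RR = 0.6: variance 0.0348, power 78%.
- μ = 4, k = 2, RR = 0.8: variance 0.0681, power 13%.

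Other combinations with μ 4 or 8, k 1 or 2 and RR 0.6 to 0.8 lie between these.

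**6. What vertigo control means.** The Vertigo section's class B covers ratios of 1 to 40, a reduction of at least 60%. The Statistical analysis section calls a reduction above 40% substantial. The Sample size and Patient safety sections name no classes, so the cut-point behind 87.5% and 67.5% cannot be read from the document.

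**The case against.** The best defence is that the Statistical analysis section, which governs the analysis, names one primary outcome, the class, and introduces the GEE only as an addition. On that reading the GEE is supportive, one test decides the trial, and 5% holds. The reading is possible, but the Abstract, the second sentence quoted from the Vertigo section, and Table 2 contradict it.

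A second defence is that a statistical analysis plan may give the testing order. It may, and the absence of detail is not the complaint. The complaint is that the published protocol makes conflicting statements about its primary outcome.

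Some stronger conclusions are tempting but not supported:

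- *That the error rate is inflated.* This follows only if success on either outcome is enough, and the protocol states no such rule.
- *That the trial is underpowered, or that 67 is wrong.* The arithmetic is right, and under proportional odds the ordinal analysis would exceed 80%.
- *That vertigo control is a third test at 0.05.* It sets the sample size and the interim limits, but no final test of it is planned, so it should not be added to the error calculation.
- *That control means classes A and B.* The document does not say so.

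**Conclusion.** The point holds in this form: the protocol labels two outcomes as primary, gives no decision rule, and bases its sample size and interim limits on a third outcome that is neither defined by class nor given an analysis.

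The 5% error rate is not assured. Under an either-wins reading it would be about 9.1% to 7.0% for assumed correlations of 0.5 to 0.9. Under a both-must-win reading it holds, at the price of joint power below that of each test. With one declared primary outcome it holds without adjustment.

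The 80% power is correct for the binary comparison and is not established for either listed primary analysis. The illustrative ranges, about 34% to 97% for the ordinal test and 13% to 78% for the count test, rest wholly on assumed inputs. They show that power depends on facts the document does not give; they are not estimates of this trial's power.

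**What to change.** 1. Name one primary outcome with one analysis. The class by ordinal mixed model is the natural candidate, since the Statistical analysis section already names it. Make the GEE rate ratio a key secondary outcome, tested only if the primary is significant. An alpha split, a both-must-win rule, or a defined binary primary outcome would also resolve the conflict, provided the sample size is justified for it.
2. Bring into line the Abstract, both sentences in the Vertigo section, the Statistical analysis text, Table 2, and the interim text under Patient safety.
3. State which classes count as vertigo control, and reconcile that with the reduction described as substantial in the Statistical analysis section.
4. Say that the 80% power refers to that binary comparison, and restate the power of the chosen primary analysis at the planned sample size, with its assumed class distribution (or rates and dispersion).

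The cost is wording in five places and one power calculation, to be done before unblinding. The downsides are that the second outcome can no longer carry the trial alone, and that the restated power may differ from 80%.

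### The analysis section's cut-off for a substantial reduction in attacks (more than 40%) contradicts the primary outcome's class B, which needs a reduction of at least 60%

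*Protocol article*

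**What the plan says.** The Vertigo section under Outcome measures defines the primary outcome as a class based on a ratio: attacks after treatment "divided by the number of attacks 6 months before treatment times 100". The scale runs from "A: Complete control of vertigo=0" through "B: Substantial control of vertigo=1–40" and "C: Limited control of vertigo=41–80" to a worst class above 120. A low score is good.

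The Statistical analysis section describes the size of effect in the other direction. It states "A decrease of 100% is considered total control of vertigo episodes" and then that "a reduction of >40% is considered a substantial and thus clinically relevant reduction". The citation there is reference 17, which the Hearing section attaches to the AAO HNS 1995 guideline. The Vertigo section names the same guideline as the source of its classes.

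Two further places rely on a responder idea. The Sample size section says that an "expected proportion of subjects achieving vertigo control of 87.5% was assumed for methylprednisolone treatment", against 67.5% on placebo. The interim rule, under Patient safety, is written in terms of between-arm differences in vertigo control. Neither place ties that term to a class or to a percentage reduction.

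**The concern.** The figure of 40 appears in both sections next to the word 'substantial', but it measures opposite things: the share of attacks left in one, the share removed in the other. The 100% anchor in the analysis sentence shows that it counts reductions, so it cannot be read as 40% remaining. It looks as though a remaining score of 40 was taken for a 40% reduction, although the article does not say so.

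The analysis sentence is the article's only numerical statement of what reduction in attacks is clinically relevant. As written, it counts as relevant some patients whom the primary outcome labels as having limited control. Anyone reporting responders or describing clinical relevance could defend either cut-off, and could do so after seeing data.

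**Working it through.** **Sample size first.** Inputs from the Sample size section: 87.5% and 67.5%, power 80%, α 5%. Sidedness is not stated; two-sided is assumed. Pooled two-proportion formula with mean proportion 0.775:

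n = [1.960 × √(2 × 0.775 × 0.225) + 0.842 × √(0.875 × 0.125 + 0.675 × 0.325)]² / 0.20²

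= [1.960 × 0.5906 + 0.842 × 0.5734]² / 0.04 ≈ 67.2 per group.

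That is 68 when rounded up, against the stated 67. With 67 per group, power is 79.9%. The arithmetic reproduces, and it does not depend on how vertigo control is defined.

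**The two cut-offs on one scale.** Reduction (%) = 100 − score. This takes the before and after counts in the same time unit, as the class limits require: the class for insignificant control, 81–120, is centred on 100, meaning no change.

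- Class B upper limit: score 40, so reduction 100 − 40 = 60%.
- Analysis sentence: reduction above 40%, so score below 100 − 40 = 60.
- Distance between the cut-offs: 60 − 40 = 20 percentage points.

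| Score (% remaining) | Reduction | Class in Vertigo section | Reduction >40%? |
|---|---|---|---|
| 0 | 100% | A | yes |
| 40 | 60% | B | yes |
| 41 | 59% | C | **yes** |
| 50 | 50% | C | **yes** |
| 59 | 41% | C | **yes** |
| 60 | 40% | C | no |
| 80 | 20% | C | no |

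The sections disagree for whole-number scores 41 to 59, about half of class C (41–80).

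**Example at the entry minimum.** The inclusion criteria require at least 4 attacks in the previous six months. With 4 before and 2 in a later six-month period, the score is 2/4 × 100 = 50. The patient is in class C in the Vertigo section and has a substantial, clinically relevant reduction in the Statistical analysis section.

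**Where the cut-off enters.** The Statistical analysis section and Table 2 list two analyses of vertigo: an ordinal mixed model over the classes, and a generalised estimating equation for attack counts that gives a rate ratio. Neither splits patients at a percentage reduction.

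**The case against.** The strongest reply is that no listed efficacy analysis uses the cut-off. Two analysts working from different sections would compute the same classes and the same rate ratio. The sentence also follows directly on the one about the rate ratio, so it may be meant as an aid to interpretation and not as a rule for classifying patients. The first part stands in full: both planned analyses of vertigo are untouched. The second does not remove the contradiction. Even as an aid to interpretation, the sentence applies the primary outcome's label to a different range and cites the same guideline for it.

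A reader might infer that vertigo control itself carries two conflicting thresholds. The text does not go that far. The analysis sentence speaks of a substantial, clinically relevant reduction, and the Sample size and Patient safety sections give vertigo control no threshold. The term is undefined there, and would stay so even if the analysis sentence were corrected.

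A reader might also infer that the looser cut-off shrinks the planned 20-point difference and costs power. The documents do not settle even the direction. As an illustration, hold the odds ratio at the planned value, (0.875/0.125) / (0.675/0.325) = 3.37, and assume that 9–13% of placebo patients fall in the disputed band (the article gives no such figure).

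- If 67.5% is the share in class A or B, placebo under the looser cut-off is 76.5–80.5%. Multiplying the odds by 3.37 gives methylprednisolone 91.6–93.3%, a difference of 15.1 to 12.8 points.
- If 67.5% is already the share with a reduction above 40%, placebo in class A or B is 58.5–54.5% and methylprednisolone 82.6–80.1%, a difference of 24.1 to 25.6 points.

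The shift changes sign with an assumption that the article leaves open. Any power figure would also concern a two-proportion test that is not among the listed efficacy analyses.

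**Conclusion.** The contradiction is real and can be read off the article without any outside source. Substantial means a reduction of at least 60% in the primary outcome and of more than 40% in the Statistical analysis section, and patients with scores of 41–59 fall between the two. This rests only on reading the score as attacks remaining in a common time unit, which the class labels make plain.

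The consequence is limited. The stated criterion for clinical relevance is wrong as measured against the trial's own classes, and so would be any responder statement built on it. The sizing assumption and the interim rule can be read either way because vertigo control is undefined there. A claim that the trial's main conclusion turns on this sentence would go too far, since neither vertigo analysis uses the cut-off. No power loss and no corrected sample size are claimed. The point should be fixed, but it does not invalidate the design.

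**What to change.** Rewrite the sentence in the Statistical analysis section to agree with the primary outcome: a score of 0 (100% reduction) is complete control, and a score of 1–40 (a reduction of at least 60%) is substantial control. If a separate threshold for clinical relevance is intended, give it a different name and its own justification.

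In the Sample size section and in the interim rule, state which classes count as vertigo control. Class A or B is the natural choice if the 87.5% and 67.5% assumptions rest on it; the sponsor should confirm this from their source. Record the definition before any unblinded look, including the planned interim analysis, so that it cannot be chosen on results.

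The cost is a few words. The planned models, data collection and sample-size arithmetic stay as they are. If the assumed proportions prove to rest on a definition other than the one adopted, the sizing assumption should be restated on the adopted definition.

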## Methods

### Trial design

In this phase 3, multicentre, double-blind, placebo-controlled randomised trial, the effect of two intratympanic methylprednisolone sodium succinate 62.5 mg/mL (Solu-Medrol in Act-O-Vial, Pfizer BV) injections 14 days apart is compared with two placebo (ie, sodium-chloride 0.9%) injections with the same time interval on vertigo attacks in patients with MD. Parallel groups will be randomly assigned to one of both arms and outcomes will be measured during a 1 year follow-up period.

To ensure transparency and completeness in this clinical trial, the SPIRIT and CONSORT checklists are provided in onlinesupplemental files 1  2.

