#### Use of escape medication and co-interventions

In case participants remain suffering from intolerable vertigo attacks, regardless of which group they are allocated to, the use of metoclopramide and co-interventions such as intratympanic injections of gentamicin or methylprednisolone will be allowed and documented during the follow-up period. This will be based on experience of participants’ vertigo frequency and shared decision making. If patients receive additional treatment, they will not be unblinded.

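### The per-protocol check on rescue drops treatment failures, more of them on placebo, and so understates the difference in vertigo control

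*Protocol article*

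**What the plan says.** The Vertigo section builds the primary class from attack counts alone: "The class of vertigo is defined by the average number of attacks per month during 6 and 12 months after treatment" is compared with the count in the six months before treatment. The classes listed run from A to E, and none of them refers to further treatment.

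The section on escape medication and co-interventions opens rescue to both arms: "In case participants remain suffering from intolerable vertigo attacks, regardless of which group they are allocated to", metoclopramide may be used and "co-interventions such as intratympanic injections of gentamicin or methylprednisolone will be allowed and documented during the follow-up period". The second drug named is the study drug, and the list is open-ended. The decision rests on the patient's experience of attacks and on shared decision making.

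Beside the intention-to-treat analysis, the Statistical analysis section names two sensitivity analyses. The first is "a per protocol analysis in which patients who received additional co-interventions to achieve vertigo control are excluded". The second is described only as "an as-treated analysis in which participants who received additional co-interventions are analysed". The incidence of escape interventions is a separate secondary outcome, analysed by logistic regression.

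The Sample size section gives the planning rates: "An expected proportion of subjects achieving vertigo control of 87.5% was assumed for methylprednisolone treatment compared with an assumed 67.5% for placebo".

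**The concern.** Patients become eligible for rescue because the two assigned injections did not control their vertigo. Removing them takes out people on the basis of the outcome under study, and the sets that remain are no longer the randomised groups. If the drug works as assumed, placebo has more failures to remove, so the exclusion flatters placebo.

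The intention-to-treat class can move the same way. A patient whose assigned injections failed, and who is then controlled by gentamicin or open methylprednisolone, can be scored A or B. There are more such patients on placebo. If the per-protocol result agrees with the intention-to-treat result, a reader will take this as reassurance about rescue, although both may be understated. At stake is how the effect of the two assigned injections is interpreted.

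**Working it through.** **Inputs.** From the Sample size section: control p = 0.875 (methylprednisolone) and 0.675 (placebo), 67 per group. The documents do not give q, the share of failures rescued. I assume 25% and 50%, first equal in both arms. I also take the planning rates as rescue-free and rescued patients as failures of the assigned injections.

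**1. The plan's own figure.** Two-sided 5%, 80% power, pooled variance: n = [1.96·√(2·0.775·0.225) + 0.842·√(0.875·0.125 + 0.675·0.325)]² / 0.20² = 67.2 per group. The stated 67 reproduces, and the sample size is not at issue.

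**2. Per-protocol set.** Rate = p / (1 − (1 − p)·q); number dropped = 67·(1 − p)·q.

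| q | Methylprednisolone | Placebo | Difference | Dropped |
|---|---|---|---|---|
| 0 | 87.5% | 67.5% | 20.0 | 0 vs 0 |
| 25% | 0.875/0.96875 = 90.3% | 0.675/0.91875 = 73.5% | 16.9 | 2.1 vs 5.4 |
| 50% | 0.875/0.9375 = 93.3% | 0.675/0.8375 = 80.6% | 12.7 | 4.2 vs 10.9 |

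These figures do not depend on the assessment window, on when rescue is given or on how well it works.

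**3. Unequal rescue.** With q = 25% on placebo, the difference returns to 20 points when 0.875/(1 − 0.125·q) = 0.9347, that is at q = 51% on methylprednisolone, about twice as often. With q = 50% on placebo it cannot return: even if every methylprednisolone failure were dropped, 100 − 80.6 = 19.4. With 25% rescued on methylprednisolone and 50% on placebo, the difference is 90.3 − 80.6 = 9.7.

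**4. A-E class regardless of rescue.** Control rate = p + (1 − p)·q·s, so the difference is 20·(1 − q·s), where s is the share of rescued failures scored A or B. Assume an unchanged attack rate before rescue, none after it, and rescue spread evenly over months 0.5 to 12. The ratio is then at most 40% if rescue comes by month 2.4 (window 0-6), 4.8 (0-12) or 8.4 (7-12).

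| Window | s | Difference, q = 25% | Difference, q = 50% |
|---|---|---|---|
| 0-6 | 1.9/11.5 = 16.5% | 19.2 | 18.3 |
| 0-12 | 4.3/11.5 = 37.4% | 18.1 | 16.3 |
| 7-12 | 7.9/11.5 = 68.7% | 16.6 | 13.1 |

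If all rescue falls in months 0.5 to 6, s is 1.9/5.5 = 34.5% (0-6) and 4.3/5.5 = 78.2% (0-12). The differences are 18.3 and 16.1 at q = 25%, and 16.5 and 12.2 at q = 50%. With equal rescue shares, the A-E and per-protocol differences both lie below 20. With rescue spread over the year and windows from month 0, the check is further from 20 than the scoring it checks. With early rescue on months 0-12 it is not.

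**5. The planned ordinal test.** Simulation: 5000 trials per case, 67 per arm, Wilcoxon test with ties. Assumed class mix: placebo A share 20, 35 or 45% with A+B = 67.5%; C/D/E 13/13/6.5%. Common odds ratio (0.875/0.125)/(0.675/0.325) = 3.37. Rescue is over months 0.5 to 12 with no attacks afterwards.

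| Scoring | Power, q = 25% | Power, q = 50% |
|---|---|---|
| A-E, months 7-12 | 90-92% | 83-87% |
| Per protocol | 91-94% | 83-89% |

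Power without rescue is 94-96%. It is still 94-96% for A-E on windows from month 0 at q = 50%, and 94-96% with rescue as a lowest level in all randomised patients. In repeat runs on months 7-12 in which 10% of the attack rate remains after rescue, A-E power is 92-96%.

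**The case against.** The strongest reply is that the per-protocol analysis is only a sensitivity analysis, the intention-to-treat result leads, and rescue by arm is reported as its own outcome, so an imbalance would be seen. All of that is true. But seeing an imbalance does not correct the control rates, and a check that is shifted by the very thing it examines is a poor choice of stated method, not a detail left to a fuller document. The as-treated analysis is described too briefly to judge, but nothing in its wording scores rescue as failure.

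The article is condensed, so a further rescue analysis may exist elsewhere. The class is also taken from a guideline that is not at hand, and any rule there on additional treatment cannot be checked. The point is therefore confined to what the article fixes. The rescue share is assumed as well. This limits the size but hardly the direction.

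Two stronger readings are tempting. A reader might infer that the primary analysis is invalid or badly underpowered. The documents do not support this: counting attacks whatever treatment follows is a legitimate intention-to-treat strategy, and step 5 shows little or no loss unless the window starts after rescue and rescued patients have no attacks at all. In that corner the loss can be larger (58-88% power if all rescue comes before month 6), but 92-95% is kept if 20% of the attack rate remains, and nothing in the protocol implies complete freedom from attacks after rescue. A reader might also infer a risk of falsely claiming benefit. With equal rescue shares the shift is towards no difference.

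**Conclusion.** The point holds for the per-protocol check. Excluding rescued patients is selection on outcome after randomisation. On the planning rates it turns 20 points into 16.9 (25% of failures rescued) or 12.7 (50%). This rests on rescued patients being failures, as the rescue provision implies, on the planning rates being rescue-free, and on methylprednisolone failures not being rescued about twice as often or more. If the planning rates already include rescue, no planned power is lost and the figures change, but the exclusion is still outcome-based.

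The A-E class may stay as it is. Because its control difference can be understated in the same direction, agreement with the per-protocol result should not be read as robustness to rescue.

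**What to change.** In the Statistical analysis section, replace the per-protocol exclusion as the main check on rescue with an analysis of the class in all randomised patients. Anyone who received a co-intervention to achieve vertigo control by that assessment goes into a lowest, not-controlled level. Count any such co-intervention, since the protocol's list is open, but not escape medication such as metoclopramide. Keep the A-E class regardless of rescue as primary, and keep the generalised estimating equation analysis of attack counts on all data. Under the assumptions above, the new analysis keeps the 20-point difference whatever share is rescued.

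The cost is one analysis sentence. Table 1 already records co-interventions at 2 weeks and at 3, 6, 9 and 12 months, and patient care does not change. The downside is that rescue decisions have no objective threshold and a patient rescued late after marked improvement ranks lowest, so this should be a sensitivity analysis only.
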